## Abstract

**Background:**

The advent of immune checkpoint inhibitors (ICIs) has powerfully broadened the scope of treatment options for malignancies with an ongoing increase of indications, but immune-related adverse events (irAEs) represent a serious threat to treatment success. Agents directed against programmed cell death protein 1 (PD-1) or its ligand 1 (PD-L1) are known to cause renal complications with an incidence of 3%. In contrast, subclinical renal involvement is estimated to be much higher, up to 29%. We recently reported about urinary flow cytometry-based detection of urinary PD-L1-positive (PD-L1^+^) kidney cells correlating with tubular PD-L1-positivity that reflected susceptibility to develop ICI-related nephrotoxicity as an irAE attending ICI treatment. Therefore, we designed a study protocol to evaluate urinary detection of PD-L1^+^ kidney cells as a tool for non-invasive biomonitoring of renal complications in cancer patients treated with ICIs.

**Methods:**

A prospective, controlled, non-interventional, longitudinal, single-center observational study will be conducted at the Department of Nephrology and Rheumatology of the University Medical Center Göttingen, Germany. We intend to enroll approximately 200 patients treated with immunotherapy from the Departments of Urology, Dermatology, and Hematology and Medical Oncology of the University Medical Center Göttingen, Germany. First, we will assess clinical, laboratory, histopathological, and urinary parameters in addition to urinary cell collection. Then, we will perform a correlative analysis between urinary flow cytometry of different PD-L1^+^ cell of renal origin with the onset of ICI-related nephrotoxicity.

**Discussion:**

Because of growing ICI-treatment applicability with an expectable incidence of renal complications, providing cost-efficient and easily performable diagnostic tools for treatment-attendant and non-invasive biomonitoring becomes vital to improve both renal and overall survival rates in cancer patients receiving immunotherapy.

**Trial registration:**

https://www.drks.de, DRKS-ID DRKS00030999.

## Introduction

With the advent of immune-checkpoint inhibitors (ICIs), the scope of cancer-treatment options has seen a powerful increment, wherein reactivation of CD8-positive T-cell cytotoxicity constitutes its functional ground (1). Established neutralizing antibodies are directed against co-inhibitory auxiliary proteins expressed on tumor cells engaging in mechanisms of so-called immune evasion. Blockade of programmed cell-death protein 1 (PD-1) and its ligand 1 (PD-L1) is associated with remarkable therapy responses, especially for solid tumor entities featuring restricted therapeutic options. Still, immune-related adverse events (irAEs) pose a serious threat to treatment success, including maintenance of tumor remission (2–6). Of these irAEs, skin, gastrointestinal, hepatic, and endocrine adverse effects are the most common (7). Kidney involvement is known to occur with an incidence ranging from 2 to 3%; subclinical affection is estimated even higher, up to 29% (8–16). Glucocorticoid therapy and discontinuation of the causative agent are the only available measures with the side effect of delayed cancer treatment. Once affected, kidneys are more prone to a renal relapse after ICI re-exposition (9–11). Nephrotoxicity related to ICI therapy mainly consists of acute interstitial nephritis (AIN) and, to a lesser extent, glomerular nephropathies (8–19). This nephrotoxicity remains unclear and deserves to be characterized regarding clinical patterns and the underlying mechanisms.

We previously reported aberrant PD-L1 expression distinct to renal compartments in ICI-related nephrotoxicity, reflecting susceptibility to develop renal irAE (20, 21). PD-L1 positivity is different in intrarenal compartments and predominantly expressed in the tubuli, which correlates with elevated serum levels of C-reactive protein (CRP) as a non-specific marker of systemic inflammation (20). Moreover, PD-L1 expression was also observed in ICI-naïve renal pathologies implying PD-L1 upregulation as an indicator of ongoing kidney damage before this becomes clinically detectable by conventional methods (20). Interestingly, urinary flow cytometry-detected PD-L1-positive (PD-L1^+^) kidney cells correlated with intrarenal PD-L1 positivity (20). Therefore, we designed a study protocol to evaluate urinary detection of PD-L1^+^ kidney cells of different origins as a tool for non-invasive and therapy-attendant biomonitoring of renal complications in cancer patients receiving immunotherapy.

## Methods

### Study design and study population

Our observational single-center study is prospective, controlled, longitudinal, and non-interventional (trial registration: https://www.drks.de, DRKS-ID: DRKS00030999). It will be performed at the Department of Nephrology and Rheumatology at University Medical Center Göttingen (UMG), Germany. In addition, cancer patients receiving ICI treatment at the Departments of Dermatology, Urology, Hematology, and Medical Oncology of the UMG will be enrolled. The type and dosing schedule of the ICI therapy will be performed as indicated by the responsible medical specialist and carried out independently from the study investigations. A sample size of 200 patients was calculated based on the reported incidences of ICI-related nephrotoxicity.

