### Sample size calculation

Due to the explorative design of the current study evaluating potential parameters that affect the risk of irAEs, the sample size calculation is not hypothesis-driven. Based on the feasibility to enroll, analyze, and follow up, a total number of 200 patients was chosen. The aim of the current study is the hazard ratio assessment of different influencing factors on irAEs related to the kidneys.

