## Discussion

Kidney affection occurring as an irAE during immunotherapy is a severe and potentially life-threatening complication endangering treatment success, hence the overall survival of cancer patients. Clinically apparent renal involvement is estimated to occur with an incidence of 3%. In contrast, previous investigations of biopsy-proven ICI-related nephrotoxicity reported a much higher frequency of up to 29% of cases implying that conventional diagnostic methods only detect advanced and pronounced kidney injury and are unable to detect early and milder forms of renal involvement (8–16). Renal biopsy is the gold standard for the etiological assignment of kidney affection but carries an increased risk of bleeding complications in the cancer-patient population. Moreover, repeated renal biopsies during a complete treatment course iteratively subject patients to the risk of hemorrhagic events. Despite discontinuing ICI treatment and steroid therapy, the kidneys stay endangered to relapse. In case of renal relapses due to cancer-treatment continuation, the clinical course may even be more fulminant, requiring kidney replacement therapy (KRT) (2). Thus, new tools for biomonitoring in clinical routine will be helpful for the early detection of complications.

Our study aims to evaluate the urinary detection of PD-L1^+^ kidney cells based on urinary flow cytometry as a non-invasive biomonitoring tool for renal complications in cancer patients treated with immunotherapy. The concept of urinary flow cytometry-based detection of renal and immune cells reflecting so-called “biosignatures” was first described for renal allograft pathology (22, 23). Adapted from receiver operating characteristics-(ROC)-curve analyses, an assignment of urinary detected cellular components and renal allograft rejection, including T-cell mediated rejection (TCMR), was enabled (22). The conceptual extension of these findings to other T-cell-mediated renal pathologies, for example, ICI-related nephrotoxicity, seems attractive. Moreover, we previously reported intrarenal PD-L1-positivity as a potential indicator of ongoing kidney damage, showing that renal irAEs correlate with detected PD-L1^+^ kidney cells in the urine (20, 21). PD-L1 upregulation was also observed in other renal pathologies implying PD-L1 functions as a response signal to injuries within the kidneys (20).

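### The protocol gives two conflicting bases for 200 patients, and its clinical incidence of 2–3% yields only about 4–6 events for a hazard-ratio aim

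*Protocol article*

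**What the plan says.** The article explains the number 200 in two places.

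- Study design and study population: "A sample size of 200 patients was calculated based on the reported incidences of ICI-related nephrotoxicity".
- Sample size calculation: "the sample size calculation is not hypothesis-driven", and then "Based on the feasibility to enroll, analyze, and follow up, a total number of 200 patients was chosen". This section names no incidence.

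The same section sets the aim: "The aim of the current study is the hazard ratio assessment of different influencing factors on irAEs related to the kidneys". Statistical methods lists Cox, logistic and Poisson regression. It adds that comparisons are neither powered nor prespecified and that no hypothesis tests are planned.

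Two levels of incidence are cited. The Introduction has "Kidney involvement is known to occur with an incidence ranging from 2 to 3%; subclinical affection is estimated even higher, up to 29" (per cent). The Discussion repeats the clinical figure, "Clinically apparent renal involvement is estimated to occur with an incidence of 3" (per cent), and attaches the higher one to biopsy series: "previous investigations of biopsy-proven ICI-related nephrotoxicity reported a much higher frequency of up to 29% of cases". Residual material of renal biopsies leaves the decision to biopsy a patient with kidney injury to the responsible nephrologist. No expected number of events and no precision for a hazard ratio is given.

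**The concern.** A size calculated from an incidence and a size chosen because it can be recruited and followed are different claims. The first tells the reader that the event rate was considered and that 200 suits it. The second makes no such claim. A reader who sees only the study design section takes away the first.

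The difference matters because the information in a hazard ratio comes from the number of events, not the number of patients. If the clinical incidence applies, very few events carry the whole aim, and the article does not say so. Declining to test hypotheses does not help here: wide intervals, and estimates that run to zero or infinity, are problems of estimation.

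**Working it through.** **1. Can 200 be reproduced?** No. The article gives no precision target, hazard ratio, number of factors or loss rate. Some common incidence-based rules, each with a target assumed for illustration, give:

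| Rule | At 2% | At 3% | At 29% |
|---|---|---|---|
| 95% CI half-width of 2 points, n = 1.96² p(1−p)/w² | 189 | 280 | – |
| 95% CI half-width of 2.5 points | 121 | 179 | – |
| 95% CI half-width of 6 points | – | – | 220 |
| 95% chance of at least one event, ln(0.05)/ln(1−p) | about 148 | about 98 | – |
| 10 expected events, 10/p | 500 | about 333 | – |

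Some fall near 200 and none equals it. The table neither identifies an origin for 200 nor excludes one.

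**2. Expected events.** The inputs are 200 patients and the incidences in the Introduction and Discussion. The assumption is that each incidence applies over the 48–52 weeks of follow-up, with no losses.

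- 200 × 0.02 = 4 (binomial 95% range 1–8)
- 200 × 0.03 = 6 (range 2–11)
- 200 × 0.29 = 58 (range 46–71)

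The chance of 10 or more events is 0.7% at 2% and 8.1% at 3%.

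**3. Precision of one hazard ratio.** The 95% interval is HR ×/÷ exp(1.96 × SE). The article states no cut-off for the urinary marker, so two forms are shown, both assumed.

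- Binary marker positive in half the patients: SE(log HR) = 1/√(D × 0.5 × 0.5), where D is the number of events.
- Continuous marker, per standard deviation: SE ≈ 1/√D.

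| Events D | SE, binary | Factor, binary | SE, per SD | Factor, per SD |
|---|---|---|---|---|
| 4 | 1.00 | 7.1 | 0.50 | 2.7 |
| 6 | 0.816 | 5.0 | 0.408 | 2.2 |
| 58 | 0.263 | 1.7 | 0.131 | 1.3 |

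For example, an estimated hazard ratio of 3 on a binary marker with 6 events has an interval from 3/4.95 = 0.6 to 3 × 4.95 = 14.9.

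**4. Risk that the estimate does not exist.** With a binary marker of prevalence p and a true hazard ratio of 1, all D events fall in one group with probability p^D + (1−p)^D. Ordinary Cox regression then returns zero or infinity.

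- p = 0.5: 12.5% with 4 events, 3.1% with 6.
- p = 0.2: 41% with 4 events, 26% with 6.

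The range is wide because the prevalence is unknown.

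**The case against.** The best defence is that the study is openly exploratory. The dedicated sample-size section gives feasibility as the reason, and Statistical methods disclaims power and testing. On that reading, the sentence in the design section is loose wording. This stands in part: lack of power is not an error here, and detectable effects at a chosen power are not the right yardstick. It does not explain why the design section attributes the number to incidences.

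A second defence is that the aim covers renal irAEs in general, so the count could approach 58. That possibility is real and must be stated. However, biopsy follows clinical judgement in cases of kidney injury, and the Discussion itself says conventional diagnostics miss early and milder forms. The article therefore does not show how subclinical cases would become counted events.

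Three stronger readings are tempting and are not supported:

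- *That incidence cannot have influenced 200.* A number can be informed by incidence and capped by feasibility, and some precision targets fall near 200. The fault is that the two sections give different bases.
- *That a joint multi-factor model is planned.* The article speaks of different factors. It does not say that they enter one model.
- *That the 29% is described inconsistently.* A lesion can be clinically silent and proven by biopsy, so the two descriptions are compatible.

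Finally, the article condenses a fuller document, so the absence of a worked calculation is not itself a defect.

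**Conclusion.** The point holds as a should-fix. The basis for 200 patients is contradicted within the article, and nothing stated ties the number to an incidence. On the article's own clinical rate, about 4–6 events are expected before losses, rising to at most about 58 if subclinical cases are ascertained and counted. With 4–6 events, a hazard ratio is known only to within a factor of about 5.0–7.1 for an evenly split binary marker, or about 2.2–2.7 per standard deviation of a continuous one.

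The event counts follow from printed figures, given that the incidences apply over the study's follow-up. The precision figures rest on the assumed form of the marker. The conclusion is not that the study is too small for an exploratory purpose. The reader is given the wrong impression of why 200 was chosen, and no indication of how little the clinical endpoint can show.

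**What to change.** 1. In Study design and study population, replace the sentence on incidences with the feasibility basis given under Sample size calculation. If an incidence did play a part, say so in both places and give the rule. Then state the expected events and precision, for example: *The number of patients was set by feasibility. At an incidence of 2–3%, 4–6 clinically apparent renal events are expected before losses; up to 58 would be expected if subclinical cases, at up to 29%, are counted. For an evenly split binary factor, the 95% interval for a hazard ratio would be the estimate multiplied and divided by about 7.1, 5.0 and 1.7 with 4, 6 and 58 events.* State which cases count as events.

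2. For clinically apparent nephrotoxicity, fit Cox models one factor at a time with Firth penalisation and profile-likelihood intervals. Penalisation keeps the estimate finite when all events fall in one group. Report the hazard ratios as exploratory, with no multi-factor claim at this event count. The detail can sit in the analysis plan.

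The cost is a less favourable stated rationale for the sample size and slightly more analysis work. No patients, visits or procedures are added.

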### Patient enrollment and study conduction

Inclusion criteria are patients 18 years or older, written informed consent, and intended immunotherapy. In addition, patients enrolled in other ongoing trials of immunotherapies with a blinded study design are considered ineligible. Within the framework of routine medical care of patients in the respective departments, eligible patients are identified and included after documented written consent. **Figure 1** shows a STROBE flow chart of the study protocol featuring an overview of inclusion and exclusion criteria. After providing written consent, a baseline visit will be conducted, where baseline demographic data, medical history, medication, and clinical symptoms will be collected. Physical examination includes the assessment of height, weight, vital parameters, general condition, the status of the integument, neck with the thyroid gland, head, ears, eyes, throat, abdomen, limbs, joints, and auscultation of the heart and lungs. Laboratory data assessments include differential blood cell counts, serum levels of sodium, potassium, calcium, creatinine, blood urea nitrogen (BUN), uric acid, aspartate aminotransferase (AST), alanine aminotransferase (ALT), gamma-glutamyl transferase, bilirubin, lactate dehydrogenase (LDH), lipase, blood glucose, creatine kinase (CK), thyroid-stimulating hormone (TSH), T3, T4, and CRP. In addition, viral serology for the human immunodeficiency virus (HIV), hepatitis A, B, and C, cytomegalovirus (CMV), and the Epstein-Barr virus (EBV) will be tested at baseline. Moreover, autoantibody testing will be performed once at baseline and afterward as clinically indicated and includes antinuclear antibodies (ANA), anti-neutrophilic cytoplasmic antibodies (ANCA), extractable nuclear antigen (ENA), anti-double stranded desoxyribonucleic acid (anti-dsDNA), anti-cyclic citrullinated peptide (anti-CCP) and rheumatoid factor (RF). In addition, urinanalysis will be performed at each visit with urine dipstick and urine sediment, and an additional asservation of 100 mL of fresh urine samples will be performed. Follow-up visits are scheduled every 12 (–16) weeks; unscheduled visits will be performed if an irAE is suspected. The end-of-study visit will be conducted after 48-52 weeks. The schedule of visits and assessments is shown in **Table 1**.

**Figure 1 f1:**
[figure not shown]
STROBE flow chart of the study protocol. ICI, immune checkpoint inhibitor; irAE, immune-related adverse event; STROBE, strengthening the reporting of observational studies in epidemiology.

**Table 1 T1:** Schedule of patient visits and assessments.

Week/occasion	0	12 (+4)	48 (+4)	Routine visits during ICI application	Non-scheduled visits (occurrence of irAE)
Written informed consent	X				
In-/exclusion criteria	X				
Enrollment	X				
Medical history	X	X	X	X	X
Physical examination^1^	X	X	X	X	X
Vital parameters^2^	X	X	X	X	X
Weight and height^3^	X	X	X	X	X
Laboratory analyses^4^	X	X	X	X	X
Urinary analyses^5^	X	X	X	X	X
Viral serologies^6^	X				
Antibody screening^7^	X				X
Medication	X	X	X	X	X
Assessment of irAE^8^	X	X	X	X	X

^1^Includes general condition, status of the integument, neck with thyroid, head, ears, eyes, throat, abdomen, limbs, joints and auscultation of heart and lungs, orienting neurological examination.

^2^Blood pressure and heart rate after five minutes of rest.

^3^Weight in kilogram, height in centimeters.

^4^Including differential blood cell count, serum levels of sodium, potassium, calcium, creatinine, BUN, uric acid, AST, ALT, gGT, bilirubin, LDH, blood glucose, CK, TSH, T3, T4, CRP.

^5^Urinary dipstick, urinary sediment, 100 mL fresh urine sample.

^6^HIV, hepatitis A/B/C, CMV, EBV.

^7^RF, anti-CCP, ANA, ENA, ANCA, anti-dsDNA.

^8^Documented on a separate data sheet.

ALT, alanin aminotransferase; ANA, antinuclear antibodies; ANCA, anti-neutrophilic cytoplasmic antibodies; Anti-CCP, cyclic citrullinated peptide; Anti-dsDNA, anti-double stranded desoxyribonucleic acid; AST, aspartate aminotransferase; BUN, blood urea nitrogen; CK, creatine kinase; CMV, cytomegalovirus; CRP, C-reactive protein; EBV, Epstein-Barr virus; ENA, extractable nuclear antigen; gGT, gamma-glutamyl transferase; HIV, human immunodeficiency virus; ICI, immune checkpoint inhibitor; irAE, immune-related adverse event; LDH, lactate dehydrogenase; RF, rheumatoid factor; TSH, thyroid-stimulating hormone.

### Asservation of urine cells

Fresh urine samples will be collected (100 mL) and loaded into an automated cytospin machine (Shandon cytospin, Thermo Scientific, Pittsburgh, USA) following the manufacturer’s instructions and centrifuged at 1000 revolutions per minute (rpm) for 10 minutes. The cell pellet is resuspended in a mixture of phosphate-buffered saline (PBS) and bovine serum albumin (BSA). Cell viability and quantity are measured in a cell counter. Urine cells are deep frozen in Gibco™ CTS™ Synth-a-Freeze™ medium at -80°C. Cells can be further processed for urinary flow cytometry.

### Flow cytometry of urinary cells

Antibody staining of cells in suspension follows standard protocols. Thawed or freshly collected cells are centrifuged at 1000 rpm at 4°C for 8 minutes. The PD-L1^+^ cell line KARPAS 299 will be used as a positive control and unstained cells as negative controls for the analysis of urinary cells. Cell suspensions are washed and resuspended in PBS and stained using antibodies against PD-L1 (APC anti-human CD274, B7-H1, PD-L1, clone 29E.2A3, Biolegend, San Diego, USA) in combination with the podocyte marker podocalyxin (anti-TRA-1-81-PE, human, clone REA246, Miltenyi Biotec GmbH, Bergisch Gladbach, Germany). Identification of tubular epithelial cell (TEC) will be done by cytokeratin (anti-cytokeratin-FITC, human, clone CK3-6H5, Miltenyi Biotec GmbH, Bergisch Gladbach, Germany) with differentiation between proximal TECs by CD-10 (CD10-PE-Vio770, human, clone 97C5, Miltenyi Biotec GmbH, Bergisch Gladbach, Germany), and distal TECs by EpCAM (CD326 (EpCAM)-APC-Vio770, human, clone HEA-125, Miltenyi Biotec GmbH, Bergisch Gladbach, Germany) (22). Cells will be incubated with antibody mixtures for 15 minutes at 4°C in the dark and gated according to positive and isotype-negative controls. For dead cell identification, propidium iodide (Miltenyi Biotec GmbH, Bergisch Gladbach, Germany) will be used to gate out non-viable cells. According to standard protocols, cells will be analyzed with the FACS Canto II machine of the cell sorting unit at the Department for Hematology and Medical Oncology of the UMG.

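### Tubular origin rests on cytokeratin in a cohort that includes Urology cancer patients, and urine cells may be run fresh or thawed, so tumour cells or handling could be read as the marker

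*Protocol article*

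**What the plan says.** All places are in the protocol article.

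- **Cell identity.** Under Flow cytometry of urinary cells: "Identification of tubular epithelial cell (TEC) will be done by cytokeratin", "with differentiation between proximal TECs by CD-10", and "distal TECs by EpCAM". Podocytes are identified separately, by podocalyxin.
- **Controls.** The same section names a PD-L1+ cell line, unstained cells and isotype controls. Cells are "gated according to positive and isotype-negative controls", and propidium iodide "will be used to gate out non-viable cells".
- **Cohort.** The Abstract (Methods) plans about "200 patients treated with immunotherapy from the Departments of Urology, Dermatology, and Hematology and Medical Oncology". The inclusion criteria under Patient enrollment and study conduction cover age, consent and planned immunotherapy, and do not mention tumour site. Figure 1, which summarises inclusion and exclusion criteria, is not shown.
- **Tumour expression.** The Introduction describes the antibody targets as "co-inhibitory auxiliary proteins expressed on tumor cells".
- **Sample state.** Asservation of urine cells says that the cells are stored frozen at -80°C. The cytometry section then begins: "Thawed or freshly collected cells are centrifuged". No rule says which samples are run in which state.
- **Visits.** Table 1 schedules urine at week 0, at follow-up, at routine visits and at unscheduled irAE visits.

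**The concern.** The study relates PD-L1+ urinary cells of renal origin to kidney toxicity, so the exposure is only as good as the assignment of origin. By the Discussion's account, the urinary-cell concept was first described in kidney transplantation. Here it is applied to cancer patients, some of them from Urology, whose urine may contain tumour epithelium. The named controls show whether a cell is alive and stains for PD-L1. They do not show whether a cytokeratin-positive cell came from a tubule or from a tumour. A patient whose tumour sheds PD-L1+ epithelial cells could then read as marker-positive with no kidney process under way, and the association with kidney events would be diluted.

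The second issue is independent of the first. Dead cells are excluded before counting, so the analysed population may differ between fresh and frozen-thawed samples. If urine from a suspected irAE is analysed the same day while routine urine waits in the freezer, part of any difference between cases and non-cases would be technical.

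**Working it through.** The plan gives no figure for assay specificity, tumour mix or fresh/thawed split, so there is nothing to reproduce. The calculations below give ranges under stated assumptions.

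**1. Expected events** (patients from Sample size calculation; incidences from the Introduction)
- Clinical: 200 × 0.02 = 4 and 200 × 0.03 = 6.
- If subclinical involvement counts, at its upper figure: 200 × 0.29 = 58.

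**2. Dilution by misread tumour cells**

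Assumptions, none from the documents: true marker prevalence 20%; 10-33% of patients have a urinary-tract tumour; 10-50% of these shed PD-L1+ cytokeratin-positive cells. The marker is treated as binary, no true positive is missed, and misread patients carry the same kidney risk as other true negatives.

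Share of true negatives misread, f = tumour share × shedding share:
- low: 0.10 × 0.10 = 0.01
- high: 0.33 × 0.50 = 0.165

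Observed RR = (0.2 × RR + 0.8f) / (0.2 + 0.8f)

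| True RR | f = 0.01 | f = 0.165 |
|---|---|---|
| 3 | (0.6 + 0.008) / 0.208 = 2.92 | (0.6 + 0.132) / 0.332 = 2.20 |
| 5 | (1.0 + 0.008) / 0.208 = 4.85 | (1.0 + 0.132) / 0.332 = 3.41 |

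The effect runs from negligible to material.

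**3. Handling linked to outcome**

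Assumptions, none from the documents: no true association; 20% of thawed samples read positive, against 30% or 40% of fresh ones.

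Positivity in a group = fresh share × fresh positivity + (1 − fresh share) × 0.20. The odds ratio compares events with non-events.

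| Fresh share, events / non-events | Fresh positivity 30% | Fresh positivity 40% |
|---|---|---|
| 50% / 50% | 1.00 | 1.00 |
| 80% / 50% | 1.17 | 1.31 |
| 80% / 20% | 1.38 | 1.78 |

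Example, last cell: events 0.8 × 0.4 + 0.2 × 0.2 = 0.36; non-events 0.2 × 0.4 + 0.8 × 0.2 = 0.24; odds ratio (0.36/0.64) / (0.24/0.76) = 1.78. With equal fresh shares there is no spurious association, only added noise.

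**4. Could modelling repair it later?**

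The marker (1 parameter), three departments (2) and sample state (1) make 4 parameters. That leaves 4/4 = 1.0 to 6/4 = 1.5 clinical events per parameter, too few for reliable adjustment. With 58 events it would be 14.5.

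**The case against.** The strongest reply is that the marker half rests on knowledge from outside the documents. Nowhere do they say that cytokeratin and EpCAM lack kidney specificity, that Urology patients have tumours draining into urine, or that shed cells survive the viability step. Figure 1 could hold a tumour-site exclusion. The Introduction also reports that urinary PD-L1+ kidney cells correlated with intrarenal PD-L1. All this stands as a limit: the point is a risk under an assumption. The reported correlation supports the assay, but the article does not say that it was tested in urinary-tract cancer.

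Four stronger readings are tempting, and the documents do not support them.

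- **The whole marker panel is unsound.** The problem lies chiefly in the parent cytokeratin population and the distal (EpCAM) subset. The podocyte population is not in question.
- **All departments are pooled without adjustment.** Statistical methods names regression families but no covariates. Covariates and strata commonly belong to the analysis plan, which is not shown, so their absence is no finding.
- **Handling does track outcome.** Nothing links sample state to visit type. The text permits such a link and does not establish it.
- **10-30% of all true negatives are misread.** In the same formula this would take a risk ratio of 3 to 2.4-1.9. But only patients with urinary-tract tumours can contribute, and the ranges above give about 1-16.5%.

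The exploratory aim is a fair argument on severity. It does not remove the point, because a misassigned cell distorts a descriptive hazard ratio as much as a test.

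**Conclusion.** The point holds as a risk that the text leaves open, not as a demonstrated bias. As written, the plan counts cytokeratin-positive urinary cells as tubular without a stated means of excluding urothelial or tumour epithelium, in a cohort whose text admits Urology patients of any tumour site. Under the assumptions in the working, a true risk ratio of 3 would appear as about 2.9-2.2 and one of 5 as about 4.8-3.4. The size depends on a tumour mix and a shedding rate that the article does not give. If Figure 1 excludes urinary-tract tumours, this half largely falls away.

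The handling half rests on the article's own text: storage is described as frozen, yet staining may start from fresh cells. The minimum consequence is noise. Bias arises only if fresh processing is more common at irAE visits. Both halves merit a change before outcome samples are analysed, because 4-6 clinical events leave little room to adjust afterwards.

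**What to change.** 1. **Sample state.** Amend the cytometry section so that all samples entering the outcome analysis are run in one state, with event and non-event samples mixed within batches and the operator blind to outcome. If both states are kept, record the state for each sample and report results by it.
2. **Tumour site.** Flag urinary-tract malignancy from the medical history, and report the association for PD-L1+ tubular cells with and without these patients.
3. **Own baseline.** Analyse change from the patient's own week-0 sample. This removes shedding that is constant over time, though not shedding that changes during follow-up.
4. **Modelling.** Do not rely on stratified or multi-covariate models for clinical events.

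The cost is low. Week-0 urine and medical history are already collected, so the change amounts to one flag and a sentence or two on handling. The downsides are some cell loss if samples are frozen, and less precision in the analysis without urinary-tract tumours. No patient's treatment is affected.
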